#### Secondary Outcomes

*Table 2* identifies the secondary outcomes and describes in detail the survey and clinical measures used to capture these constructs. Specifically, secondary outcomes include the following: (1) psychological well-being (depressive symptoms, perceived stress, positive and negative affect, optimism, emotional vitality, life engagement and meaning, happiness-inducing behavior, and social support), (2) healthy behaviors (physical activity, diet, sodium intake, smoking status, sleep quality and duration, and mediation use), and (3) biological materials (serum blood spots).

#### Antecedent Variables and Qualitative Data

In addition to the main outcomes of interest, we will also collect variables hypothesized to be antecedents or important confounders when exploring intervention effects. The list of antecedents or covariates is summarized in Table 2 and includes the following: (1) demographic factors, (2) anthropometric measurements, (3) acculturation, (4) level of religiosity, (5) self-reported mental and physical health, and (6) current or previous history of medical comorbidities. In addition, we will conduct qualitative exit interviews to capture facilitators and barriers in using the tablet computer to access *¡Alégrate!* curricular content. Indeed, qualitative process evaluation techniques further inform metrics of acceptability and utility for the modality of content distribution. Finally, we will also analyze data describing the overall use of the website by trial participants, including the number of website logins per participant, average length of screen time per site visit, and extent to which enrollees completed and recorded practicing of at-home exercises.

**Table 2 table2:** Outcome, mediator, and intervention-based measures.

Measure					Description
**Outcomes (exams 1 through 3 unless otherwise noted)**					
	**Primary outcomes**				
		**Blood pressure measurements**			
			Sitting blood pressure	We will use an automatic sphygmomanometer to evaluate sitting BP. This measurement device has been validated across multiple cohort studies including MESA, NHANES, and HCHS/SOL [44,45]. The 3 systolic and diastolic blood pressure readings will be taken with participants in the seated position; mean values will be obtained by averaging the last 2 readings	
			24-hour ambulatory blood pressure	An ambulatory BP monitoring (ABPM) method will be used to capture 24-hour daytime and nighttime BP readings in the natural environment (CONTECTM Automatic Blood Pressure Monitor [ABPM50]); this device has shown adequate reliability and accuracy [46]. We will consider 24-hour mean systolic and diastolic readings. Weighing 1.87 lbs, the ABPM monitors will be fitted and pretested before 24-hour use [47]	
	**Secondary outcomes**				
		**Psychological well-being**			
			Depressive symptoms	The 20-item Center for Epidemiologic Studies Depression Scale (CES-D) will be used to measure depressive symptomatology [48]. The CES-D uses a 4-point Likert scale to probe the extent to which an individual has been troubled by depressive symptoms in the last 7 days; scores range from 0 to 60	
			Perceived stress scale (PSS)	The PSS includes 10-items to assess self-perceived levels of stress over the previous month using a Likert scale ranging from never to always [49]. Previously validated in the HCHS/SOL cohort [50], overall scores range from 0 to 40 for the full scale and includes items such as, “How often have you felt confident about your ability to handle your personal problems?”	
			Positive and negative affect	Participants will be asked to recall emotions experienced in the past week using a modified version of the Differential Emotions Scale [51]. A list of 26 different emotions will be provided (eg, grateful, happy, guilty, relieved, ashamed, or humiliated) and participants will be asked to identify how often they have experienced each on a scale ranging from 1—Not at all to 9—All the time	
			Dispositional optimism	The revised Life Orientation Test (*LOT-R*) will be used to assess dispositional optimism. The LOT-R is a validated 6-item self-administered questionnaire with possible scores ranging from 0 (least optimistic) to 24 (most optimistic) [52,53]. The scale includes 3 positively worded items and 3 negatively worded items that are rated on a 5-point Likert scale	
			Emotional vitality	Emotional vitality is characterized as a sense of overall well-being through active engagement in day-to-day activities and effectual regulation of emotions. Borrowing items from the General Well-being Schedule, this construct will be captured using a 6-item measure previously used in published studies with available evidence of adequate psychometric properties [54,55]. Respondents are asked to think about the previous 30 days, and using an ordinal scale are instructed to rate statements such as, “Has your daily life been full of things that were interesting to you?” and “Have you been feeling emotionally stable and sure of yourself?”	
			Life engagement and meaning (LET)	The LET is a 6-item instrument that probes the extent to which an individual engages in activities which they personally value and find meaningful [56], for example, *To me, the things that I do are all worthwhile.* Scores range from 6 to 30 with respondents rating items on a 5-point scale. Higher scores characterize an individual that experiences greater life engagement and purpose	
			Happiness-inducing behavior	This 38-item survey inquires of the extent to which participant engage in behavior or prescribed strategies known to induce happiness, for example, relaying gratitude, engaging in mediation and religious practices, focusing on positive life events, among others [57]	
			Self-perceived social support	The Medical Outcomes Study Social Support Survey will be used to quantify social support as provided by family, friends, and acquaintances [58]. This 20-item instrument first directs participants to quantify the total number of close friends and relatives they possess, that is, defined as the people they feel at ease with and can talk about what is on their mind. Remaining items ask participants to rate statements using a 5-point Likert scale that inquire of the perceived availability of support from family, friends, or others, if or when needed. Sample statements include “someone you can count on to listen to you when you need to talk” and “someone to help with daily chores if you were sick”	
		**Healthy behaviors**			
			Physical activity and dietary intake	Items of the Summary of Diabetes Self-Care Activities Measure will be used to assess engagement in physical activity and self-reported dietary intake. Items ask participants to report engagement across activities over a 7-day period and include queries such as, “On how many of the last SEVEN DAYS did you participate in at least 30 minutes of physical activity?” and “How many of the last SEVEN DAYS have you followed a healthful eating plan?”	
			Sodium intake	The Scored Sodium Questionnaire will be used to measure dietary intake specifically targeting quantification of sodium consumption [59]. Participants will be asked to report dietary patterns over the last 7 days across multiple food groups (eg, breads, processed meats, tinned or packet soups) with response options indicating daily consumption to rare or never eaten items. Dietary intake will also include items of the Summary of Diabetes Self-Care Activities questionnaire [60]	
			Smoking status	Participants will identify whether they are current smokers, former smokers, or if they have never smoked before. Current smokers will report the average number of cigarettes they smoke per day	
			Self-reported sleep quality and duration	Two self-report items were used to capture subjective rating of sleep. The first inquired about the number of hours per night of sleep (ie, during the main sleep period) that participants were getting on weekdays or workdays. The second asked participants to rate their typical night’s sleep during the past 4 weeks, with a Likert response option ranging from *very sound or restful* to *very restless*	
			Medication use and adherence	Participants will be asked if they were prescribed oral medication for their high blood pressure. Those indicating use of antihypertensive medication will be asked to identify the start date when they first initiated said use. We will also document whether participants had taken their blood pressure medication on the date of their clinical visit, and if so, the approximate time of day. Finally, medication adherence specific to antihypertensive drugs will be assessed using the Morisky Medication Adherence Scale [61]. At each scheduled assessment, participants will be instructed to bring all medications currently taken. Research staff will document details across medication (eg, dosage) and they will save a digital picture of associated pill bottles	
		**Markers of cardiovascular disease**			
			Serum blood spots	Serum blood spots will be collected from each participant at baseline and immediately postintervention (8 weeks). A trained research staff will prick the participant’s middle or ring finger using sterile procedures. After wiping away the first spot of blood, 5 subsequent drops will be collected using Whatman #903 filter paper. The blood spots will be stored for future analysis in a −20° freezer at the Institute for Minority Health Research at the University of Illinois at Chicago	

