### Study Procedures

#### Recruitment

Participants were recruited from a single Federally Qualified Health Center (FQHC) located in Chicago and situated in a neighborhood with a high density of Hispanic/Latino residents. The attending physician and clinical staff (eg, registered nurse, medical assistant) identify potentially eligible patients and subsequently refer them to *¡Alégrate!* research staff who then follow-up via phone or in person; participant information is stored in a secure web-based portal. During phone or in-person exchanges, the staff inform participants that the goal of the study is to explore whether an intervention intended to boost positive emotions results in better cardiac-related health. Only initial eligibility is determined via phone, with an in-person visit scheduled to establish full eligibility based on sitting B*P* values. Research staff will also approach patients in the waiting area to provide information about the research study and offer an invitation to receive a no-cost BP screening; research staff will collect contact information of those expressing interest to determine full eligibility. The consent form and study materials outline the design of the study and inform participants of random assignment into 1 of 2 groups, either the group where *they learn skills known* to *boost mood and heighten positive emotions* or the group where *they would report experiences of positive or negative emotions on a thrice weekly basis*. It is communicated that all curricular instruction occurs online by visiting our *¡Alégrate!* website. In addition, the staff inform participants that 3 in-person clinical visits are required, each 2 to 3 hours in length, where staff collect survey and clinical data including anthropometric information, blood spots, and 24-hour BP monitoring; home visits are also offered for data collection to increase rates of retention. Participants are informed that they can keep the investigator-purchased tablet computer at the end of the study as compensation for their participation and time invested [36]. To reduce the risk of bias, enrollees in both the treatment and control arms keep the tablet computer at the end of study participation, that is, immediately after providing follow-up survey and clinical data at 12 weeks postbaseline. Participants expressing interest in enrolling in the trial who are screened for full eligibility and ultimately qualify undergo a face-to-face consent process and complete the survey and clinical exams before randomization.

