
#### Consent, Assessments, and Randomization

Survey and clinical exams occur in tandem at 3 time points, as follows: Time 1 (baseline) at study enrollment; Time 2, immediately postintervention (5 weeks after baseline); and Time 3 (12 weeks after baseline). Figure 1 details the design of the study and the associated timeline for recruitment, enrollment, and assessment tasks.

Survey and clinical assessments are conducted in Spanish through in-person interviews by trained bilingual research staff in a one-to-one encounter at the participating FQHC. Questionnaires used and associated constructs assessed as part of the survey interview includes measures of psychological well-being (eg, optimism, positive affect), acculturation, self-reported health and medical comorbidities, engagement in healthy behaviors (eg, sodium intake, sleep quality, and duration), and medication adherence. Many survey instruments used in the current trial have undergone previous psychometric testing, showing adequate validity and reliability in the Spanish language. For those not previously translated, our team conducted thorough forward and backward translation procedures to craft a Spanish-language adaptation with linguistic equivalency. All survey data were collected using REDCap, a secure internet-based platform for building and managing web-based surveys. Finally, clinical examinations will be carried out by research staff to collect anthropometric data (eg, body mass index, waist-to-hip ratio), serum blood spots, sitting BP, and 24-hour ambulatory BP profiles. It should be noted that all data will be deidentified, stored in a password-protected computer, and/or stored in a locked cabinet in the principal investigator’s office.

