### Content of Control Sessions

Participants randomly assigned to the active control condition will be asked to visit the study site where they report their emotions (eg, grateful, happy, guilty, relieved, ashamed, etc), 3 times weekly, using the Differential Emotions Scale (DES), but they will not be granted access to curricular content of our *¡Alégrate!* positive psychological intervention. It takes 5 to 10 min to complete the DES online. Emotion reporting for the control condition occurs for the duration of the active intervention period, that is, 5 weeks in total. Research has previously established effectual use of emotion reporting as a control condition, with documented benefits similar to that of a placebo effect, and with high rates of retention (approximately 80%). Concerted efforts are undertaken to promote retention among participants in the control arm, including postcard notices and phone calls to remind participants to engage in web-based emotion reporting and to appear, in person, for scheduled clinical assessments. Finally, participants in the control condition will be granted access to the web-based *¡Alégrate!* curricular content upon completion of their final follow-up assessment at 12 weeks postbaseline.

Participants in both the treatment and control arms will receive detailed handouts on how to operate the *Samsung Galaxy Tab A* tablet computer, along with instructions on connecting to Wi-Fi and accessing the *¡Alégrate!* website. Handouts display textual instructions along with detailed step-by-step visual screenshots, along with a listing of Wi-Fi locations in the local neighborhood, for example, coffee shops and public libraries or bookstores. In addition, staff will hold, in person, 15- to 20-min tutorials at baseline to familiarize enrollees on tablet use, with the assurance of continual availability via phone or in person to assist with any issues and to troubleshoot difficulties encountered with the technology.

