### Planned Analyses

The primary outcome of the *¡Alégrate!* trial focused on prospective changes in B*P* values, that is, both sitting BP and 24-hour ambulatory readings. The first aim was to examine the efficacy of the intervention in reducing B*P* values immediately postintervention (ie, 5 weeks) and at the 12-week follow-up period, that is, Exams 2 and 3. The second aim was to explore whether the intervention leads to significant improvements in psychological well-being and greater adherence to healthy behavioral practices. We will additionally test whether psychological well-being and healthy behaviors serve as mediators when exploring intervention effects on BP control. The third aim is to test intervention effects on circulating markers of inflammation, specifically high-sensitivity C-reactive protein.

Descriptive statistics, at baseline, will summarize participant characteristics for the full sample and stratified by intervention arm. Bivariate tests will be conducted to compare the intervention and control conditions to ensure compatibility across key variables (eg, demographic factors, well-being profiles, etc) and to test the success of the randomization protocol. Discrepancies in baseline values across conditions will inform covariates for inclusion when testing our main hypotheses of interest. In addition, we will document the number of missing observations over time to assess the potential for bias resulting from significant dropout and differential attrition by condition. We will perform independent sample two-tailed *t* tests and/or Fisher exact tests to compare baseline characteristics of enrollees who completed the trial versus those who prematurely dropped out, allowing us to test possible predictors of attrition.

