#### Aim 3: Evaluate Intervention Effects on High-Sensitivity C-Reactive Protein

Similar analytic techniques as previously described will be used when testing intervention effects on chronic inflammation. Specifically, the term capturing Group×Time interaction will test whether lower levels of inflammation are evident at 8 weeks postbaseline for the intervention group versus the active control arm.

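### Aim 3's follow-up blood spot and C-reactive protein test are dated week 8, but the course ends at week 5 and no week-8 visit is scheduled

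*Protocol article*

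**What the plan says.** In the protocol article, Table 2 (Markers of cardiovascular disease, Serum blood spots) gives two collection times: "Serum blood spots will be collected from each participant at baseline and immediately postintervention (8 weeks"). The Aim 3 analysis uses the same week. Its Group×Time term is to test whether "lower levels of inflammation are evident at 8 weeks postbaseline for the intervention group versus the active control arm".

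The rest of the article sets a different calendar:

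- Consent, Assessments, and Randomization lists three time points. The first is baseline, and the other two are "Time 2, immediately postintervention (5 weeks after baseline); and Time 3 (12 weeks after baseline").
- Planned Analyses places the blood pressure comparisons "immediately postintervention (ie, 5 weeks) and at the 12-week follow-up period, that is, Exams 2 and 3".
- Content of Control Sessions fixes the length of the course: "Emotion reporting for the control condition occurs for the duration of the active intervention period, that is, 5 weeks in total".
- Recruitment says that "3 in-person clinical visits are required" and describes them as the visits "where staff collect survey and clinical data including anthropometric information, blood spots, and 24-hour BP monitoring".
- The outcomes header of Table 2 sets the default schedule as "exams 1 through 3 unless otherwise noted".
- Aim 1 codes time in the mixed model as 0, 5 and 12. Aim 2 runs its Group×Time test at 5 weeks.

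**The concern.** The blood-spot entry attaches the label immediately postintervention to week 8, whereas the assessment schedule and Planned Analyses attach it to week 5. The label and the week cannot both be right. Aim 3 then repeats week 8 without the label, so read alone it is a plain instruction to test at a time when no exam takes place.

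Under Table 2 there is a single follow-up sample, so its date defines the quantity that Aim 3 estimates. At week 5 that is the effect on inflammation at the end of the course, with blood pressure and the surveys measured at the same visit. At week 8 it is the effect 3 weeks after the course, with no blood pressure or survey data from that time. If the conflict stays, staff and analysts may follow different schedules, and a later reader could not tell whether a week-5 result was prespecified or a departure from the plan.

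**Working it through.** **Inputs**

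| Item | Value | Where in the protocol article |
|---|---|---|
| Follow-up blood spot | week 8, labelled immediately postintervention | Table 2, Serum blood spots |
| C-reactive protein test | week 8 after baseline | Aim 3 |
| Immediately postintervention | week 5, Exam 2 | Consent, Assessments, and Randomization; Planned Analyses; Aim 1 heading |
| Course length | 5 weeks | Overview and Study Design; Content of the Intervention; Content of Control Sessions |
| In-person visits | 3 | Recruitment |
| Model times | t = 0, 5, 12 | Aim 1 |
| Planned enrolment; attrition | 70; 20% | Abstract; Planned Analyses |

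**1. Is week 8 an exam?** The scheduled set is {0, 5, 12}, and 8 is not in it. None of the 3 exams falls at week 8.

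**2. How far off is it?**
- Exam 2: 5 × 7 = day 35. Exam 3: 12 × 7 = day 84. Week 8: 8 × 7 = day 56.
- Gap from Exam 2: 56 − 35 = 21 days. Gap to Exam 3: 84 − 56 = 28 days.
- Time since the end of the course: 8 − 5 = 3 weeks.

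The gap is too wide to pass as a loose visit window around either exam.

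**3. Does the Table 2 header allow it?** The header lets a row depart from the default, so blood spots may be taken at fewer than three exams. It does not create a visit that the Recruitment and Consent sections exclude. The home visits offered under Recruitment are an alternative setting for data collection and add no time point.

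**4. Does the analysis model allow it?** Aim 3 says it uses techniques like those already described. Those use t = 0, 5, 12, so there is no week-8 value to enter.

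**5. Which figure is isolated?** Eight weeks appears in two places, Table 2 and Aim 3. The 5-week course or exam is stated in at least eight sections: Abstract; Overview and Study Design; Consent, Assessments, and Randomization; Content of the Intervention; Content of Control Sessions; Planned Analyses; Aim 1; Aim 2.

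**6. Cost of keeping week 8.** One further visit each: 70 × 1 = 70 at most. If the whole 20% attrition allowance had already occurred by week 8 (an assumption, since attrition by week is not given), 70 × 0.8 = 56.

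**7. Is the sample size touched?** No. With one baseline, two follow-ups and ρ = 0.60, the covariance-adjusted variance factor is (1 + 0.60)/2 − 0.60² = 0.44. Then n = 2 × [12 × (1.960 + 0.842)/6]² × 0.44 = 27.63, or 28 per arm as stated. Allowing for 20% attrition, 28/0.8 = 35 per arm, 70 in total. C-reactive protein plays no part in this.

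**The case against.** The strongest reply is that this is a wrong number beside a correct label. Immediately postintervention points to one visit, Exam 2, and Recruitment lists blood spots among the data collected at the clinic visits. In practice staff would probably take the sample at week 5. That is the likelier intention, and the first remedy below adopts it. It does not settle the matter, because the same week recurs in the Aim 3 analysis, where no label points back to Exam 2.

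Two further points stand in part. First, that there is only one follow-up sample rests on the Table 2 entry. The Recruitment and Consent sections do not limit blood spots to two visits, so a 12-week sample is not clearly excluded. Such a sample would still not supply a week-8 value. Second, data collection was ongoing when the article was written. If some samples really were taken near week 8, changing the number alone would misdate them, so actual collection dates have to be recorded.

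That an article condenses the full protocol is no answer here. Nothing is said to be missing; two stated times conflict.

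**Conclusion.** The concern holds. Week 8, given for the follow-up blood spot and for the C-reactive protein test, contradicts the article's own schedule: it matches none of the three exams and lies 3 weeks after the course ends. As written, Aim 3 cannot be carried out on the stated calendar. The consequence is limited to secondary Aim 3; the primary blood pressure analysis and the sample size are unchanged. It should be corrected, since the error affects both sampling and analysis of a named aim. The conclusion rests on the text, because Figure 1, the timeline, was not available. The reading that week 5 was meant is an inference from the rest of the article.

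**What to change.** Change 8 weeks to 5 weeks in the Serum blood spots entry of Table 2 and in Aim 3, so that the sample is taken and C-reactive protein tested at Exam 2 with blood pressure and the surveys (t = 0, 5). For samples already taken, record each actual collection date and check it against Exam 2 before finalizing the wording. State in the same entry whether a 12-week sample is taken. If samples were taken at Exam 2, the cost is two wording corrections and no extra visit.

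If week 8 is really intended, add that visit to the Recruitment and Consent, Assessments, and Randomization sections and to the consent information, and describe it as 3 weeks after the course ends. The cost is then a fourth visit for up to 70 participants, about 56 under the attrition assumption above, and a consent change.
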